## Abstract

**Background:**

Preterm birth is the most common cause of neonatal morbidity and mortality. Postponing delivery for 48 hours with tocolytics to allow for maternal steroid administration and antenatal transportation to a centre with neonatal intensive care unit facilities is the standard treatment for women with threatening preterm delivery in most centres. However, there is controversy as to which tocolytic agent is the drug of first choice. Previous trials have focused on tocolytic efficacy and side effects, and are probably underpowered to detect clinically meaningfull differences in neonatal outcome. Thus, the current evidence is inconclusive to support a balanced recommendation for clinical practice. This multicenter randomised clinical trial aims to compare nifedipine and atosiban in terms of neonatal outcome, duration of pregnancy and maternal side effects.

**Methods/Design:**

The Apostel III trial is a nationwide multicenter randomised controlled study. Women with threatened preterm labour (gestational age 25 – 34 weeks) defined as at least 3 contractions per 30 minutes, and 1) a cervical length of ≤ 10 mm or 2) a cervical length of 11-30 mm and a positive Fibronectin test or 3) ruptured membranes will be randomly allocated to treatment with nifedipine or atosiban. Primary outcome is a composite measure of severe neonatal morbidity and mortality. Secondary outcomes will be time to delivery, gestational age at delivery, days on ventilation support, neonatal intensive care (NICU) admittance, length admission in neonatal intensive care, total days in hospital until 3 months corrected age, convulsions, apnoea, asphyxia, proven meningitis, pneumothorax, maternal side effects and costs. Furthermore, an economic evaluation of the treatment will be performed. Analysis will be by intention to treat principle. The power calculation is based on an expected 10% difference in the prevalence of adverse neonatal outcome. This implies that 500 women have to be randomised (two sided test, β 0.2 at alpha 0.05).

**Discussion:**

This trial will provide evidence on the optimal drug of choice in acute tocolysis in threatening preterm labour.

**Trial registration:**

Clinical trial registration: NTR2947, date of registration: June 20th 2011.

## Background

Preterm birth is the most common cause of neonatal morbidity and mortality worldwide [1]. In the USA, the rate of infants born before 37 weeks gestation is 12-13%; while in Europe and other developed countries these rates vary between 5-11% [2,3]. Preterm birth accounts for approximately 75% of all neonatal deaths and 50% of childhood neurological morbidities [4,5] and puts a financial burden on the public health care system [6]. Neurodevelopmental impairments are frequently present in preterm infants, and are associated with gestational age [7]. Neonatal outcome is enhanced by antenatal corticosteroid administration and in-utero transfer to a tertiary care centre [8,9]. To optimize outcome in threatening preterm delivery, postponing delivery for 48 hours with tocolytic agents is common practice in most perinatal centres [10], to allow maximal effect of maternal steroid administration and transportation of the mother to a centre with neonatal intensive care unit (NICU) facilities.

Several types of tocolytic drugs are commonly used as treatment in preterm labour. These include the β adrenoceptor agonist ritodrine hydrochloride, the oxytocin receptor antagonist atosiban and the calcium channel blocking agent nifedipine. Several meta-analyses indicate that tocolytic drugs are superior to placebo or other tocolytics at delaying delivery by 48 hours and 7 days [11,12].

However, controversy exists as to which tocolytic is the drug of first choice. The ideal drug of choice should be efficient in postponing preterm labour, have a favorable safety profile in both mother and fetus, and should reduce neonatal morbidity and mortality at a reasonable cost.

Studies on β adrenoceptor agonists have shown mixed results for postponing delivery compared to placebo [13]. As β adrenoceptor agonists have substantial side effects, use has been largely abandoned from clinical practice. A Cochrane review on calcium channel blockers for inhibiting preterm labour showed that nifedipine significantly reduced delivery within seven days of receiving treatment as compared with any other tocolytic agent (relative risk (RR) 0.76; 95% confidence interval (CI) 0.60 to 0.97) [14]. In addition, as compared to other tocolytics, calcium channel blockers also reduced the frequency of neonatal respiratory distress syndrome (RR 0.63; 95% CI 0.46 to 0.88), necrotising enterocolitis (RR 0.21; 95% CI 0.05 to 0.96), intraventricular haemorrhage (RR 0.59 95% CI 0.36 to 0.98) and neonatal jaundice (RR 0.73; 95% CI 0.57 to 0.93), and the requirement for women to have treatment ceased for adverse drug reaction (RR 0.14; 95% CI 0.05 to 0.36). The Cochrane review on oxytocin receptor antagonists for inhibiting preterm labour failed to demonstrate the superiority of atosiban over β adrenoceptor agonists (RR 0.98; 95% CI 0.68 to 1.41) or placebo (RR 2.5; 95% CI 0.51 to 12.35) in terms of tocolytic efficacy or infant outcomes [15]. On the other hand, atosiban is thought to be completely safe for the mother, whereas nifedipine may cause severe hypotension and fetal death [16]. Such side effects could however not be demonstrated in a previous nationwide study in The Netherlands [17]. Two small studies did not show a difference in effectiveness between nifedipine and atosiban [18,19], however, more side effects were observed with the use of nifedipine, consisting of hypotension, tachycardia headache and vertigo. Neonatal outcome was not reported in one study, the other study did not show a difference.

Recently, a larger study was published, (n = 145) and found fewer failures within 48 hours for atosiban compared with nifedipine [20]. However, nifedipine was associated with a longer postponement of delivery. Neonatal morbidity was comparable between the two groups, although the number of neonatal admissions to the NICU and length of postnatal hospital admission was significantly higher in the atosiban group as compared with the nifedipine group. The main outcome measure of these 3 trials were tocolytic efficacy and tolerability, but the trails may be underpowered to detect clinically meaningfull effects in neonatal outcome. Therefore, the evidence remains inconclusive to support a balanced recommendation for clinical practice as the ultimate goal of tocolysis is not only to postpone delivery, but to improve neonatal outcome. This multicenter randomised clinical trial aims to compare nifedipine and atosiban in terms of neonatal outcome, duration of pregnancy, maternal side effects and costs. The study is conducted within the Dutch Obstetric Consortium, a collaborative effort of obstetric clinics in The Netherlands to perform clinical trials.

## Methods/Design

### Aims

The objective of this study is to compare the effectiveness of the tocolytic agents nifedipine and atosiban in the improvement of neonatal outcome in women with threatened preterm labour with a gestational age between 25 – 34 weeks. Outcome is measured in terms of neonatal mortality and morbidity (chronic lung disease, severe intraventricular haemorrhage, periventricular leucomalacia, culture proven sepsis, necrotizing enterocolitis), gestational age at delivery, maternal side effects and costs.

### Participants/eligibility criteria

We included women with a high risk of preterm birth. Women, aged ≥18 years, with threatened preterm labour and a gestational age between 25 and 34 weeks are eligible for participation in the Apostel III trial. The diagnosis of threatened preterm labour is defined by uterine contractions, at least 3 contractions per 30 minutes, and one of the following: 1) a cervical length of ≤10 mm or 2) a cervical length of 11-30 mm and a positive Fibronectin test or 3) ruptured amniotic membranes. Patients with singleton or twin pregnancies are eligible, independent of the position of the fetus.

Exclusion criteria are presence of a contra-indication for tocolysis (severe vaginal bleeding, signs of fetal distress or intrauterine infection, hypertension or use of anti-hypertensive medication, myocardial infarction (<1 month), unstable angina pectoris), cerclage, > 5 cm cervical dilatation, neonates suspected of chromosomal or structural anomalies and tocolytic treatment for >6 hours prior to arrival in a participating centre.

### Procedures, recruitment, randomization and collection of baseline data

The study will be a nationwide multicentre randomised controlled trial conducted within the Dutch Obstetric Consortium. The Dutch Obstetric Consortium is a research collaboration of obstetric clinics in the Netherlands. All 10 Dutch perinatal centres with NICU facilities will participate in the trial. In addition, 10 large teaching hospitals in the Netherlands and 2 perinatal centres in Belgium will participate in this trial.

Eligible women will be identified by the staff and/or local research coordinator of the participating hospitals. After counselling and reading the patient information form, patients will be asked for written informed consent. We will provide patient information in Dutch and English. After informed consent, baseline demographics, obstetric and medical history of patient will be entered in a web-based database, which will also facilitate randomisation. Randomisation will be performed by a web based computerized program using permuted-block randomisation. Randomisation allocation will be in a 1:1 ratio for Nifedipine or Atosiban, block size will be 4.

As this is a comparison of oral medication and intravenous medication, and as both group are treated with active medication, the study will not be blinded.

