### Statistical issues

#### ***Sample size***

The sample size is calculated based on a 10%- reduction of the composite poor neonatal outcome from 25% in the atosiban arm to 15% in the nifedipine arm. With a beta of 0.2 and alpha of 0.05 we have to randomize 500 patients (250 in each arm).

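### A single fixed block size of 4 in an open-label trial leaves an opportunity for selection at enrolment, with between about 0.07% and 33.3% of allocations inferable with certainty, depending on whether blocks run within centre

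*Protocol article*

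**What the plan says.** All the relevant statements stand in one section of the protocol article, on procedures, recruitment, randomization and collection of baseline data.

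- Method: "Randomisation will be performed by a web based computerized program using permuted-block randomisation".
- Ratio and block length: "Randomisation allocation will be in a 1:1 ratio for Nifedipine or Atosiban, block size will be 4". One size is given, with no mention of variation.
- Masking: one drug is oral and the other intravenous, so "the study will not be blinded".
- Who recruits: "Eligible women will be identified by the staff and/or local research coordinator of the participating hospitals".
- Order of events: "After informed consent, baseline demographics, obstetric and medical history of patient will be entered in a web-based database, which will also facilitate randomisation".
- Centres: "All 10 Dutch perinatal centres with NICU facilities will participate in the trial", and in addition "10 large teaching hospitals in the Netherlands and 2 perinatal centres in Belgium will participate in this trial", making 10 + 10 + 2 = 22.

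The article does not say whether the blocks run within each centre or along one list shared by all of them. It also does not say whether sites are told the block length.

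**The concern.** In a 1:1 block of 4, each arm has two places. Once one arm has used both, the rest of the block is fixed. Treatment is open, so staff see each allocation made at their own hospital. Anyone who knows the block length and the earlier allocations in the current block can sometimes deduce the next arm.

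Web allocation hides the list but not this deduction. Issuing the allocation only after consent does not prevent it either, because the deduction can be made earlier, when staff decide whether to approach a woman.

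At stake is the prognostic balance of the arms. The Background section calls the choice of first-line tocolytic controversial and reports differing safety concerns for the two drugs, so individual preferences are plausible, though none is documented. The trial enrols between 25 and 34 weeks, and the Background links impairment in preterm infants to gestational age. If invitations depended on the expected arm, the arms could differ in baseline risk. Intention to treat preserves the groups as randomised, but it cannot correct for who was selected into them.

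**Working it through.** **The plan's own figure.** The article gives no predictability figure. Its only related number is the sample size, set for a fall "from 25% in the atosiban arm to 15% in the nifedipine arm" with two-sided alpha 0.05 and power 0.80:

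n per arm = [1.96·√(2·0.20·0.80) + 0.8416·√(0.25·0.75 + 0.15·0.85)]² / 0.10² = 249.98, so 250 per arm and 500 in all.

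This matches the article and is not affected by the present point.

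**Case A: blocks within centre, all earlier allocations in the block known.** There are 6 equally likely orders: AABB, ABAB, ABBA, BBAA, BABA, BAAB.

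| Place in block | Probability that the allocation is certain | Probability that the best guess is right |
|---|---|---|
| 1 | 0 | 1/2 |
| 2 | 0 | 2/3 |
| 3 | 2/6 = 1/3 (AABB, BBAA) | 1/3·1 + 2/3·1/2 = 2/3 |
| 4 | 1 | 1 |

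- Certain share = (0 + 0 + 1/3 + 1)/4 = 33.3%, and 500/3 ≈ 167 women.
- Best-guess success = (1/2 + 2/3 + 2/3 + 1)/4 = 17/24 = 70.8%, against 50% by chance.

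**Case B: one list for all centres, staff see only their own.** Let s be a centre's share of recruitment. An allocation is certain for its staff only if the two earlier like allocations in that block were both made at that centre, which has probability s².

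- Place 3: (1/3)·s². Place 4: s², because the first three places always contain exactly one like pair.
- Certain share = (s²/3 + s²)/4 = s²/3.
- Equal recruitment, s = 1/22 (assumption): 1/(3·484) = 0.07%, or 0.34 of 500 women.
- A large centre, s = 20% (assumption): 0.04/3 = 1.3% of that centre's allocations.

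Case B credits staff with knowing where blocks begin, which is hard on a shared list, so these values are upper limits under its assumptions.

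**What the certain share could do (illustration; the risk shifts are assumptions).** Suppose staff act only on certain allocations and enrol women whose baseline risk is d points above or below 20%, according to the arm they expect. The spurious arm difference is 2·d·(certain share).

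- Case A, d = 1: 2·1·1/3 = 0.7 points. Case A, d = 3: 2·3·1/3 = 2 points, one fifth of the 10-point target.
- Standard error at 250 per arm: √(2·0.20·0.80/250) = 3.58 points. A 2-point shift is 0.56 standard errors and would raise the two-sided type I error from 5% to about 8.6%. A 0.7-point shift would raise it to about 5.4%.
- Case B with s = 1/22, d = 3: 2·3·0.0007 = 0.004 points, which is nil in practice.

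**Alternatives under the Case A assumption.** The fixed sizes are exact. The mixed sizes come from a simulation of lists of 24, in which staff know the set of sizes in use and the start of the list, but not the size of each block.

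| Block sizes | Certain | Best guess right |
|---|---|---|
| 4 fixed | 33.3% | 70.8% |
| 6 fixed | 25.0% | 68.3% |
| 8 fixed | 20.0% | 66.6% |
| 4 and 6 mixed | about 6% | about 69% |
| 4, 6 and 8 mixed | about 2% | about 67% |

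Mixing nearly removes certainty. It lowers best-guess success only a little, because any balanced block rewards betting on the arm that is behind.

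**The case against.** The strongest reply is that the one-third figure rests on a structure the article does not describe. It mentions no stratification by centre, only one web program serving 22 centres. On a single shared list the certain share is roughly 500 times smaller (33.3% against 0.07%). The deciding detail may stand in the full protocol, and its absence from a condensed article is no fault. This stands, and it is why the size must be given as a range.

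Three further replies carry some weight:

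- Women enter with active contractions, and more than 6 hours of prior tocolysis excludes them. There is little room to delay an invitation, although withholding one remains possible.
- At about 23 women per centre (500/22), staff would have to keep track of block boundaries.
- No staff preference is documented, and no bias in the primary outcome can be estimated from the article.

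A reader might infer that recruiting staff know every earlier allocation, so that the fourth in each block is always known to them. The documents do not support that: open treatment reveals the allocations at one's own hospital, not at 21 others. A reader might also take the printed block length as proof that sites knew it while recruiting. The article does not say what sites were told, or when it appeared relative to recruitment.

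These replies do not rescue the choice itself. The fixed size is stated, not omitted, and nothing in the section rules out blocks within centre.

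**Conclusion.** The point holds as an avoidable weakness of uncertain size. The end points of the range are 33.3% certain allocations if blocks run within centre and staff follow them, and about 0.07% if one list serves 22 equally recruiting centres and staff see only their own. The arithmetic is exact under each assumption. Which assumption applies is not stated, so confidence in the practical importance is moderate.

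The stronger conclusion, that allocation in this trial was predictable or its enrolment biased, does not follow. The documents show an opportunity, not its use. The illustrated shifts of 0.7 to 2 points depend on assumed behaviour and apply only to blocks within centre.

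**What to change.** For all allocations still to be made, replace the single block size of 4 with sizes that vary at random (for example 4 and 6, or 4, 6 and 8). Generate them centrally and do not disclose them to sites until recruitment ends. The size already printed cannot be withdrawn, so the change helps only future allocations. It would also help to state whether blocks run within centre, since that settles where in the range the trial lies.

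The cost is a setting in the web program and one sentence. The largest possible imbalance in an unfinished block rises from 2 women to 3 (size 6) or 4 (size 8) per list. Even an assumed overall split of 240 to 260 keeps 4·240·260/500² = 99.8% of the information of an equal split, so the loss at 500 women is negligible. As the last table shows, the gain is mainly the removal of certain allocations; some ability to guess remains under any blocked scheme.

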### Interventions

Patients are allocated to nifedipine or atosiban for 48 hours. In the nifedipine group, the initial dose will be 2 × 10 mg nifedipine capsules orally in the first hour, followed by 20 mg nifedipine retard per 6 hours for the next 47 hours. In the first hour after starting nifedipine, blood pressure and heart rate will be measured every 15 minutes. If blood pressure remains within the normal limits, treatment will be continued and blood pressure and heart rate will be measured 4 times every 24 hours.

In the atosiban group, a bolus injection of 6.75 mg i.v. in 1 minute, followed by 18 mg/hour for 3 hours, followed by a maintenance dosage of 6 mg/hour for 45 hours.

Antenatal corticosteroids will be administered according to the clinical guideline. Prophylactic treatment with antibiotics is at the decision of the attending physician. When the attending physician considers escape medication, this can be discussed with a perinatologist who will be available for study questions 24 hours per day.

### Outcome measures

#### ***Primary outcome measures***

The primary outcome measure will be a composite of adverse neonatal outcome, including bronchopulmonary dysplasia (BPD), periventricular leucomalacia (PVL) > grade 1, intraventricular haemorrhage > grade 2, necrotising enterocolitis (NEC) > stage 1 [21], culture proven sepsis and in-hospital death.

The diagnosis of BPD will be made according to the international consensus guideline as described by Jobe and Bancalari [22] at time of discharge home or at 36 weeks of corrected gestational age. PVL > grade 1 and intraventricular haemorrhage > grade 2 will be diagnosed by repeated neonatal cranial ultrasound by the neonatologist according to the guidelines on neuro imaging described by de Vries [23] and Ment et al. [24] NEC will be diagnosed according to Bell [21], > stage 1. Culture proven sepsis is diagnosed on the combination of clinical signs and positive blood cultures.

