#### ***Secondary outcome measures***

Secondary outcomes will be time to delivery, gestational age at delivery, days on ventilation support, length of admission in neonatal intensive care, convulsions, apnoea, asphyxia, proven meningitis, pneumothorax, total days in hospital until 3 months corrected age. Furthermore we will examine differences in maternal mortality and maternal side effects leading to discontinuation of study medication.

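### As worded, the primary composite does not count a fetal death between randomisation and birth, although the protocol names fetal death as a possible, contested harm of nifedipine

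*Protocol article*

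**What the plan says.** Under Primary outcome measures: "The primary outcome measure will be a composite of adverse neonatal outcome". The components are bronchopulmonary dysplasia, periventricular leucomalacia, intraventricular haemorrhage, necrotising enterocolitis, "culture proven sepsis and in-hospital death".

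Two other places describe the same endpoint. The Methods/Design part of the Abstract says: "Primary outcome is a composite measure of severe neonatal morbidity and mortality". The Aims say: "Outcome is measured in terms of neonatal mortality and morbidity".

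Among the secondary outcomes, the only item on death concerns the mother: "Furthermore we will examine differences in maternal mortality and maternal side effects leading to discontinuation of study medication". Stillbirth, fetal death and perinatal death appear in neither outcome list.

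The Background contrasts the safety of the two drugs and says "nifedipine may cause severe hypotension and fetal death". The next sentence qualifies this: "Such side effects could however not be demonstrated in a previous nationwide study in The Netherlands".

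Women are randomised at 25 to 34 weeks of gestation, before birth. The Data analysis section commits to intention to treat.

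**The concern.** Randomisation precedes birth, so death in utero is a possible outcome of the randomised comparison. A stillborn child cannot develop any of the five morbidities in the composite. If the death component covers only deaths after live birth, the plan leaves two ways to handle a stillbirth: score it as free of a primary event, or drop it from the analysis. The first places the worst possible result among the good outcomes. The second removes a randomised pregnancy because of something that happened after allocation.

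This matters more here than in most trials. Fetal death is a harm that the protocol itself mentions for one arm, and that arm is the one the sample size assumes will do better (15% against 25%). The same outcome also drives the indicative interim criterion and the cost per prevented case in the economic evaluation. The trial is unblinded, so a scoring rule left open could be settled with the allocation known.

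**Working it through.** **Reading the definition**

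| Place | Wording of scope | Fetal death covered? |
|---|---|---|
| Abstract, Methods/Design | neonatal morbidity and mortality | no |
| Aims | neonatal mortality and morbidity | no |
| Primary outcome measures | adverse neonatal outcome; in-hospital death | not on the natural reading; the bare words are ambiguous |
| Secondary outcome measures | maternal mortality only | no |

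No section says how a pregnancy ending in fetal death is scored.

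**The plan's own figure.** Inputs from Sample size and the Abstract: 25% against 15%, two-sided alpha 0.05, power 80%. The pooled two-proportion formula gives n per arm = [1.96·√(2·0.20·0.80) + 0.8416·√(0.25·0.75 + 0.15·0.85)]² / 0.10² = (1.1087 + 0.4724)² / 0.01 ≈ 250, or 500 in total. The stated sample size reproduces and is not in dispute.

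**What one death does.** Counting a death instead of scoring it as a non-event changes the arm's rate by 1/250 = 0.4 percentage points.

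**Illustration at equal underlying risk.** Assumptions, none from the documents except the 25% and the 250: *f* fetal deaths with nifedipine and none with atosiban, one fetus per woman, and 25% risk in both arms for all others. Events among the others are (250 − *f*)·0.25. The nifedipine risk is then:

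- non-event: (250 − *f*)·0.25 / 250
- excluded: (250 − *f*)·0.25 / (250 − *f*)
- counted: [(250 − *f*)·0.25 + *f*] / 250

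Dividing by 0.25 gives the relative risk, nifedipine against atosiban:

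| *f* | Non-event | Excluded | Counted |
|---|---|---|---|
| 1 | 0.996 | 1.000 | 1.012 |
| 5 | 0.980 | 1.000 | 1.060 |
| 8 | 0.968 | 1.000 | 1.096 |

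For *f* = 5, for example: 245·0.25 = 61.25 events; 61.25/250 = 24.5%; 61.25/245 = 25.0%; 66.25/250 = 26.5%.

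**If the fetuses lost were at higher risk.** Take the extreme case in which each would otherwise have had a primary event. With *f* = 5, 62.5 − 5 = 57.5 events remain. The relative risk is 57.5/250/0.25 = 0.920 as non-events, 57.5/245/0.25 = 0.939 if excluded, and 62.5/250/0.25 = 1.000 if counted. Exclusion is no longer neutral.

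**Under the planned rates.** With *f* = 5 and 15% risk for the remaining 245, there are 36.75 events. The nifedipine risk is 14.7% as non-events, 15.0% if excluded and 41.75/250 = 16.7% if counted. Power against 25% is 0.825 with non-event scoring and 0.628 with counting.

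In every scenario computed, leaving the deaths out gives nifedipine a lower relative risk than counting them.

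**The case against.** Several points on the other side are sound.

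- **The words are not explicit.** The death component is not itself qualified as neonatal, so a fetal death in an admitted woman could be argued to fit. This stands as an ambiguity. But the composite's label, the Abstract and the Aims all point to neonatal deaths, and a fetal death outside hospital would be missed on either reading.
- **The harm is contested.** The Background reports that a nationwide study did not demonstrate it. This stands. The number of deaths may be small and the numerical effect modest.
- **The direction of bias is not fixed.** A reader might infer that the definition must favour the arm that causes fetal deaths. That holds if they are scored as non-events, or if they are excluded and the fetuses lost were at higher risk. With exclusion at equal risk the relative risk is 1.000. The documents do not say which scoring applies.
- **The monitoring committee is not blind to the harm.** A reader might infer that fetal deaths are hidden at the interim look. The documents do not support that. Serious adverse events are reported to the committee, it may call an extra analysis or end the trial, and the p < 0.005 criterion is only indicative. What remains is that fetal deaths would not enter that criterion or the final primary comparison.
- **An article condenses the full protocol.** Coding details may well stand elsewhere. But the point concerns the primary definition that the article does state, not a missing detail. If a fuller document already counts fetal death, the article's wording contradicts it and needs aligning.

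**Conclusion.** The point holds. On its natural reading the primary endpoint does not count an intrauterine death after randomisation, and no secondary outcome picks it up. Scored as a non-event, such a death lowers the arm's rate. If excluded, it is neutral at equal underlying risk, but the harm is uncounted and the set analysed is no longer the set randomised.

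The size cannot be taken from the documents, which give no fetal death rate. The firm figure is arithmetic: 0.4 percentage points per death in an arm of 250, assuming one fetus per woman, although twins are eligible. Five deaths in one arm would make 5/250 = 2 points between counting and non-event scoring, against a planned difference of 10. That is a chosen illustration and not an expectation. With exclusion the gap to counting is 16.7% − 15.0% = 1.7 points.

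A reader might also infer that deaths must be followed to a later fixed age, such as the 3 months corrected age used for hospital days. That is a separate preference. The defect lies before birth, and repairing it needs no change of horizon.

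**What to change.** Reword the death component in the Abstract, the Aims and Primary outcome measures as perinatal death: any fetal death after randomisation, or infant death before hospital discharge. State that every fetus alive at randomisation stays in the denominator. Report fetal and neonatal deaths separately as components, so that a reader can see which of them drives any difference.

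The cost is an amendment to the endpoint wording, best made before outcome data are seen by arm. Follow-up of women and infants already provides for recording delivery details in the case report form, so no new data collection or longer follow-up should be needed. The downside is that the endpoint broadens slightly from neonatal to perinatal, so the name of the composite should change with it.
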